### Aim 1: determine the effects of training condition (CM, LC, DE) on training outputs (i.e., clinician knowledge, skill, and attitude)

#### Analyses

We hypothesize that the greatest improvements will be found for clinicians in the CM group followed by LC, clinic staff trained by clinicians in CM and LC groups, and DE (in that order). We will use the change scores on the following Ford-Weissbein [71] training outcomes: Coaches Quiz, Competence Check, and Coach Coding. Because training is at the clinician level, we will compute the change scores for each clinician and then compare the treatments using those changes. We recognize that the clinicians are nested within organization and will include that in our regression model, along with any other covariates that are associated with outcomes. We will use the one-way analysis of variance (ANOVA) to compare the change scores between the four groups. And because we have stated an ordered alternative (e.g., CM better than LC), we will use Bartholomew’s test which is powered for ordered alternatives unlike the usual F test, which is an omnibus test. Later, we will test the cascading effect of the CM model in comparing the performance of "second generation" CM clinicians to other clinicians in other conditions (CM-generation one, DE, LC). 

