#### Clinicians

To be eligible, clinicians were (a) currently employed at a clinic selected to participate in training, (b) a masters or doctoral level professional in the human services field (e.g., social work, psychology, education), (c) licensed in his/her field OR receiving supervision from a licensed individual, (d) actively seeing children and families who are appropriate for PCIT (e.g., age, behavior problem severity), (e) receptive to training but not previously trained in PCIT, and (f) amenable to study tasks (e.g., video taping, completing assessments).

Based on experience with implementation studies [76, 77] and high mental health workforce turnover [78, 79], we anticipated that few clinicians will leave the training or withdraw from the study (e.g., we had a retention rate of 96 % (187/195) for clinicians in a similar trial). However, we anticipate that up to 35 % of clinicians will leave their clinics (e.g., resign) or change jobs within their clinic during the course of the study [77]. Using an intent-to-train model, clinicians who leave their clinic will remain in the study, but we may lose some clinic and client level data unless the clinician goes to another clinic that is already participating in the study or providing PCIT. All efforts have been made to get full data, but clinic level ethical, fiscal, and logistical details (e.g., FWAs, IRB protocols) may prohibit full data collection at a new site.

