### Training conditions

The experimental manipulation in this study was within the Training Design of the Training Transfer Conceptual Model [71]. Table 1 highlights key similarities and differences across groups. Trainers were balanced across conditions. Consistent across each training condition was treatment content (i.e., treatment manual, coding manual, and workbook) and consultation with a trainer.

**Table 1 Tab1:** Condition comparison on key design features

Feature	LC	CM	DE
Primary level targeted	Multiple (senior leader, supervisor, clinician)	Clinician	Clinician
Unique features	1. Addressing multiple organizational levels within the organization that might impact implementation,	1. A “top-down,” hierarchical training approach (EBT expert to a community supervisor to trainees within the community clinician’s organization),	1. Broad public health impact,
	2. Organizing “core teams” (i.e., workgroups) within each organization,	2. Strong and specific focus on two trainees who are advanced clinicians, and	2. Easy access to interactive training program online
	3. Emphasizing cross-site sharing among teams,	3. Extensive use of in vivo skill modeling, direct practice, observation and feedback within the clinic setting.	3. Revieing materials is self-paced, independent, and can be repeated
	4. Utilizing a quality improvement process, which focuses on measuring and monitoring incremental improvements		
Ultimate goal	Create a learning organization	Focus on fidelity	Make training accessible
Trainers—number	3 + admin support	2	1
Trainers—expertise	PCIT, Program Development	PCIT	PCIT
Trainees—number per site and role within organization	2–5 members comprise a “core team.” Minimally include clinicians and supervisors.	2 senior clinicians who also treat families	Unlimited
Training group size (approx)	20 participants from 6 agencies	12 participants from 6 agencies	Unlimited
Training components/ structure	Pre-work phase	5-day initial training;	Web-based training + materials
	3 2-day Learning Sessions	2-day training 6 months after the initial training	
	Action periods between learning sessions		
Time in workshop training	6 days	7 days	None
Consultation (group)	2 h per month	2 h per month	2 h per month
Time frame	12 months	12 months	12 months
Training site	Offsite	Offsite	On-site
Videotape review and feedback	Minimum four tapes per trainee by within agency supervisor	Minimum four tapes per trainee by PCIT expert	None

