### Outcome measures and assessment procedures

The three primary outcomes of interest are training, implementation, and client outcomes. A review of outcomes measures across participants and timepoints is provided in Table 2.

**Table 2 Tab2:** Assessment measures across timepoints and participants

Construct	Measure	Brief description	Timepoints	Participant(s)	Method
Training outputs					
Knowledge					
	The PCIT Coaches Quiz [96]	22-items to assess clinicians’ knowledge of PCIT concepts and coaching scenarios; mixed question format of multiple choice and short answer	Baseline	Supervisors	Self-report
			12 months	Clinicians	
			24 months		
Skill					
	PCIT Therapist Competency Checklist	17-item checklist of PCIT competency criteria based on established PCIT Training Guidelines	Ongoing	Completed by the trainer on clinicians	Live Behavior observation
	FIRST Coach Coding System [97]	Assesses the quality and style of a therapist’s coaching	Ongoing	Completed by the trainer on clinicians	Video review behavior observation
	Supervisor Impressions of Competence in PCIT [98]	Supervision structure, practice, content, and skill	6 months	Completed by the supervisors on clinicians	Supervisor Report of clinician behavior
			12 months		
			24 months		
Attitude					
	Training Satisfaction [99]	Satisfaction with on-site training materials, content, and trainer	During each on-site training	Supervisors	Self-report
				clinicians	
	Treatment Satisfaction	Satisfaction with the treatment, concerns or barriers to using PCIT, and suggestion for improving its relevance	6 months	Supervisors	Self-report
			12 months	Clinicians	
			24 months		
	Usage Rating Profile—Intervention [100]	35-item measure of intervention usage, including acceptability, understanding, feasibility, and system support	6 months	Supervisors	Self-report
			12 months	Clinicians	
			24 months		
	PCIT Learning Experience Feedback Form	8-item survey to assess satisfaction with PCIT training	6 months	Administrators	Self-report
			12 months		
			24 months		
Training inputs					
Trainee characteristics					
	Demographic Information Form	Basic demographic and contact information	Baseline	Administrators	Self-report
				Supervisors Clinicians	
	Treatment Provider and Practices Survey [101]	Demographic information and variables hypothesized to affect adoption of EBTs	Baseline	Supervisors Clinicians	Self-report
Training design					

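### Aim 1 analyses change scores on two trainer-rated skill measures for which Table 2 lists no baseline and no fixed time, contrary to the general assessment schedule

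*Protocol article*

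**What the plan says.** The Aim 1 Analyses section names three outcomes: "We will use the change scores on the following Ford-Weissbein [71] training outcomes: Coaches Quiz, Competence Check, and Coach Coding". It then fixes their use: "we will compute the change scores for each clinician and then compare the treatments using those changes". The conditions are compared by ANOVA, with Bartholomew's test for the stated ordering that puts CM first, then LC, and DE last.

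Table 2, under Outcome measures and assessment procedures, describes the measures as follows.

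- Coaches Quiz: "22-items to assess clinicians’ knowledge of PCIT concepts and coaching scenarios; mixed question format of multiple choice and short answer". It is a self-report at baseline, 12 and 24 months.
- PCIT Therapist Competency Checklist: "17-item checklist of PCIT competency criteria based on established PCIT Training Guidelines". Its timing, rater and method cells read "Ongoing Completed by the trainer on clinicians Live Behavior observation".
- FIRST Coach Coding System: "Assesses the quality and style of a therapist’s coaching". It is also listed as ongoing and completed by the trainer, by video review.

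The Methods/design text says that clinician-level training outcomes, observational ones included, are assessed at baseline, 6, 12 and 24 months. The abstract gives the same four times for practice skills.

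**The concern.** A change score needs a defined start and a defined end. For the Competency Checklist and Coach Coding, Table 2 supplies neither, while the text implies both. An analyst holding only ongoing ratings would probably take the first one as the start. That rating comes after training has begun, and after a different kind and amount of training in each arm. Part of the effect under study would then be subtracted, in unequal parts.

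The ratings are also made by the people who deliver the training. The hypothesis is a stated ordering of the conditions, and the chosen test is sensitive to that ordering, so a timing or rating difference linked to condition acts directly on the tested contrast. These two are the only skill measures among the three outcomes that Aim 1 names.

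**Working it through.** The article gives no sample size, power, effect size or standard deviation for Aim 1, so there is no stated figure to reproduce. The check sets the sections side by side.

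**1. Schedule of each named outcome**

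| Aim 1 outcome | Table 2 timing | Table 2 rater | Abstract and Methods/design text |
|---|---|---|---|
| Coaches Quiz | baseline, 12, 24 months | self-report | baseline, 6, 12, 24 months |
| Competence Check (Competency Checklist) | ongoing | trainer, live | baseline, 6, 12, 24 months |
| Coach Coding (FIRST) | ongoing | trainer, video | baseline, 6, 12, 24 months |

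By Table 2, 1 of 3 outcomes has a listed baseline and fixed follow-up times, and 2 of 3 have neither. By the text, all 3 have a baseline. The two accounts conflict.

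Competence Check is matched to the Competency Checklist by name. If the Supervisor Impressions of Competence were meant, the rater would be the supervisor and the times 6, 12 and 24 months, but a baseline would still be missing from the table.

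**2. Which account is more plausible?** Table 2 names a baseline where a measure has one, and none of its three Skill rows does. Clinicians had to be "receptive to training but not previously trained in PCIT". Families are recruited after clinician training begins, from those with whom clinicians are using PCIT. No pre-training PCIT session that a trainer could rate is evident. This favours the table but does not prove it.

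**3. What precedes a first ongoing rating.** CM begins with 40 hours of face-to-face training, LC with a 3-month pre-work phase, and DE with online modules of about 10 hours. Table 1 gives 7, 6 and no workshop days for CM, LC and DE. Live observation by a trainer has obvious occasions in CM; for DE, the trainer contact described is telephone consultation.

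**4. Effect on the contrast.** In arm a, let G be the true skill gain at follow-up, f the fraction reached before the first rating, and d any drift in the rater's leniency between first and last rating. Then

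observed change in arm a = G_a(1 − f_a) + d_a

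CM minus DE = (G_CM − G_DE) − (f_CM·G_CM − f_DE·G_DE) + (d_CM − d_DE)

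Assume, for illustration only, that both arms gain 1 SD, so the true difference is 0.

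- f_CM from 0 to 0.5 and f_DE = 0, no drift: apparent difference from 0 to −0.5 SD, against CM.
- f_CM = 0 and f_DE from 0 to 0.5 (DE clinicians first rated late), no drift: from 0 to +0.5 SD, in favour of CM.
- Rater expectation that raises later CM scores adds a positive term, which can cancel or reverse the first case.

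None of these values comes from the article. They show only that the sign is not determined.

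**5. Levels at a common time.** With r the rater's leniency at follow-up, the difference in levels is (G_CM − G_DE) + (r_CM − r_DE), taking pre-training skill as balanced in expectation by randomization. The fractions f drop out. Constant leniency, which cancels in a change score, does not cancel here, so a comparison of levels needs scoring without knowledge of condition.

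**The case against.** The strongest reply is that the article does state a baseline for practice skills and observational training outcomes, and that the ongoing entry in Table 2 may be shorthand for a repeated rating. A journal article may also leave exact rating windows to the full protocol. This stands to the extent that a reader should not infer that no baseline exists, or that the change scores cannot be computed: a baseline may have been collected, and a first-to-last change can always be formed. It does not remove the conflict between table and text, or the dependence of a first rating on arm.

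A reader might also infer from Table 1 that DE has no skill ratings, because the tape-review row shows "Minimum four tapes per trainee by within agency supervisor" for LC, an expert for CM and none for DE. That row describes training feedback. Elsewhere the article says that all clinicians had to accept videotaping and that clinician evaluation relied on submitted recordings, with no restriction by arm. Research coding in DE is therefore not ruled out.

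That the raters are unblinded is an inference from their role; the article is silent on masking. It does say that trainers were balanced across conditions, which limits confounding of rater severity with arm but does not conceal the condition.

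Finally, if untrained clinicians all score at the floor, change and level differ only by a constant, and a true baseline adds nothing. That is correct, and it means that little is lost by comparing levels.

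**Conclusion.** The point holds as an internal contradiction with a consequence for the analysis. For 2 of the 3 Aim 1 outcomes, the change score is undefined as written and not timed alike across clinicians or arms. If the first ongoing rating becomes the baseline, the contrast absorbs unequal amounts of early training, and raters who presumably know the condition may add to this or offset it.

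The size and net direction are unknown. The illustrative half standard deviation in either direction is an assumption and should not be cited as an estimate. The conclusion rests on matching Competence Check to the Competency Checklist, and on no pre-training rating having been taken. If one was taken in every arm, the remaining work is to list it, fix the follow-up times and state how the ratings are masked.

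**What to change.** Reconcile the abstract, the Methods/design schedule, Table 2 and the Aim 1 Analyses section before the data are analysed.

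- If a true pre-training rating exists in all three arms, list it in Table 2 with the follow-up times and use it as a covariate.
- If not, drop change scores for the Competency Checklist and Coach Coding. Compare levels in common windows, for example around 12 and 24 months, from submitted session recordings chosen by the same rule in every arm.
- Have existing trainers score recordings of clinicians whom they did not train, without the condition label. Report missing recordings by arm.
- Analyse the Coaches Quiz with its collected baseline as a covariate.

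The cost is plan wording and some re-assignment of scoring. Live-observation ratings become descriptive. Equal numbers of recordings per clinician cannot be guaranteed: all four training waves had started, and the Practical and operational issues section reports barriers to submitting recordings.

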**Methods/design:**

This study (NIMH RO1 MH095750; ClinicalTrials.gov Identifier: NCT02543359), which is currently in progress, will evaluate the effectiveness of three training models (Learning Collaborative (LC), Cascading Model (CM), and Distance Education (DE)) to implement a well-established EBT , Parent-Child Interaction Therapy, in real-world, community settings. The three models differ in their costs, skill training, quality control methods, and capacity to address broader implementation challenges. The project is guided by three specific aims: (1) to build knowledge about training outcomes, (2) to build knowledge about implementation outcomes, and (3) to test the differential impact of training clinicians using LC, CM, and DE models on key client outcomes. Fifty (50) licensed psychiatric clinics across Pennsylvania were randomized to one of the three training conditions: (1) LC, (2) CM, or (3) DE. The impact of training on practice skills (*clinician level*) and implementation/sustainment outcomes (*clinic level*) are being evaluated at four timepoints coinciding with the training schedule: baseline, 6 (mid), 12 (post), and 24 months (1 year follow-up). Immediately after training begins, parent–child dyads (*client level*) are recruited from the caseloads of participating clinicians. Client outcomes are being assessed at four timepoints (pre-treatment, 1, 6, and 12 months after the pre-treatment).

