### Procedures

#### Randomization

Counties with at least one participating clinic located in the county were randomized to study condition [82]. Randomization occurred at the county level for two reasons. First, the state in which the study is being conducted is a commonwealth that is “state administered and county controlled” meaning that there is considerable variability in how counties implement mental health policies. Given that this project, like any EBT implementation, will require clinics to develop new programs and possibly rely on the larger system/context of which they are a part of, there could be substantial variability for implementation across counties. For example, establishing a referral base likely will impact implementation outcomes and will be different across counties. Given that this variability would be difficult to quantify, our goal has been to balance across conditions through the randomization procedure. Second, it is not logistically or financially possible to train all clinics at once. If we were to randomize clinics to a condition it is probable that within one county, we would have multiple training conditions occurring at different times. This could affect the previous training condition, particularly for smaller counties where clinics might have close communication or even share clinicians. Similar to previous trials that have randomized at the county level [82, 83], randomization of county to condition was balanced on key covariates including population size (urban/ rural) and poverty level [84].

Training occurred through four waves because it would be impossible to train all clinics at the same time. Given these constraints, we used SAS to write a routine for the randomization. Within training wave 1, counties were randomized to one of two conditions. Within waves 2, 3, and 4, counties were randomized to one of three conditions. The two conditions implemented in wave 1 were randomly chosen from the three conditions. The reason for this change was because wave 1 occurred early in the study when recruitment was beginning, and fewer counties had agreed to participate by study deadlines. Wave 1 included 5 clinics located in 2 counties. Wave 2 included 18 clinics located in 12 counties. Wave 3 included 13 clinics located in 4 counties. Wave 4 included 14 clinics located in 12 counties.

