### Aim 3: evaluate improvement for parent–child dyads treated by clinicians across training conditions, and explore the influence of multi-level moderators (clinician characteristics, work environment) and mediators (fidelity) of treatment gains

#### Analyses

We hypothesize that improvements will be greater for parent–child dyads treated by clinicians in the CM condition followed by LC, clinic staff trained by clinicians in the CM group, and DE (in that order). Our basic approach will be to use ANOVA methods as in Aim 1 but with proper accounting of the nesting of dyads. We expect, on average, approximately one dyad per clinician; however, whenever we have more than one dyad for a clinician we will use the data from those dyads to estimate the associated variance component, which in turn we can use to test the fit of our model. In order to examine multi-level moderators and mediators of treatment, we will use the standard framework of Baron and Kenney [88] and as elaborated by Kraemer et al. [89] to test for moderators and mediators. We regard these analyses as exploratory because tests of interactions are often not as powerful as those for main effects.

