### Trial status

To date, all four waves of training have been initiated. Training efforts and clinical consultation will continue through 2016. County and clinic recruitment is now complete, with 50 clinics, representing 37 randomization units enrolled in the study, which is lower than the originally predicted enrollment of 72 clinics [91]. From participating agencies, 100 clinicians, 50 supervisors, and 50 administrators have been enrolled. Additionally, 26 “second generation” clinicians have been enrolled and will continue to be enrolled as the study progresses. At the time of the manuscript acceptance (9/16/15), 203 families had consented to participate in the study; 198 families had completed the baseline assessment. Family enrollment is expected to continue through December 31, 2016, and it is anticipated that family enrollment will surpass the target of 288. Thus far, retention rates have varied across participant types but have remained high. As indicated above, we anticipate a 96 % retention rate for professional participants; to date, 94 % of professionals have been retained. We anticipate an 88 % retention rate for families; to date, 95 % of families have been retained. Likewise, data collection thus far has yielded assessment completion rates of 93 % for professional participants and 86 % for families. A few study team decisions have influenced these rates: (1) we kept in the study all clinicians who left their original agencies and (2) (if possible) we included families from these clinicians who were seen in new agencies. We recognize that these rates currently are within or surpass the expected range; however, it is early in the study timeline, and many things likely will affect final rates.

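### The main Aim 1 and Aim 3 test mixes a never-allocated fourth group with the three randomized conditions, and rejection by the ordered test does not by itself show CM better than LC

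*Protocol article*

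**What the plan says.** The abstract says that the clinics "were randomized to one of the three training conditions". The Randomization section makes the county the unit: "Counties with at least one participating clinic located in the county were randomized to study condition".

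The Analyses text under Aim 1 ranks four groups, with CM first, "followed by LC, clinic staff trained by clinicians in CM and LC groups, and DE (in that order"). It then states the test: "We will use the one-way analysis of variance (ANOVA) to compare the change scores between the four groups". The reason given for the ordered test is that "because we have stated an ordered alternative (e.g., CM better than LC), we will use Bartholomew’s test". The same paragraph ends with a separate, later comparison of second-generation CM clinicians with first-generation CM, DE and LC clinicians.

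The Analyses text under Aim 3 also ranks four groups, with CM first, but words the third place differently: "followed by LC, clinic staff trained by clinicians in the CM group, and DE (in that order"). It uses the ANOVA methods of Aim 1, adjusted for the nesting of dyads.

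The Learning collaborative and Cascading model sections show where the extra group comes from. After the first 12 months of training, selected LC staff and the CM trainees are prepared to train colleagues in their own organizations. No such step is described for DE. Trial status reports 26 second-generation clinicians, who "clinicians have been enrolled and will continue to be enrolled as the study progresses".

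**The concern.** Randomization protects comparisons among LC, CM and DE. Second generation was not a condition to which any county was assigned. The group arises only in CM and LC clinics, and only after their training year. Placing it in the main test as a fourth level turns one p-value into a mixture of randomized and non-randomized contrasts, and a significant result could come from the non-randomized part.

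The second difficulty concerns what rejection means. The article motivates Bartholomew's test by the example of CM being better than LC. Rejection shows only that the means are not all equal, in favour of an order with at least one strict step. A reader could take significance as support for the whole ranking, CM over LC included, when the data show only that DE is low. CM versus LC is one of the three comparisons the randomization was set up to answer.

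**Working it through.** **Inputs from the article.** Three randomized conditions (abstract, Randomization). Four groups in the test (Aim 1). 100 clinicians, 50 supervisors and 26 second-generation clinicians enrolled (Trial status). The article gives no alpha, effect size, SD or power for this test, so there is no design figure to reproduce.

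**1. Counting the groups.**
- Aim 1 heading: three conditions.
- Aim 1 test: four groups (CM, LC, CM- and LC-trained staff, DE).
- Aim 1 closing sentence: a later test of second-generation CM clinicians.
- Aim 2 costs: three groups.
- Aim 3: four groups (CM, LC, CM-trained staff, DE), with no stated place for dyads of LC-trained second-generation staff.

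The only way to reach four in Aim 1 is to include second-generation staff. If the later sentence means that they are kept out of the main test, the count of four is wrong.

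**2. Size of the extra group.** 26/(100 + 26) = 20.6% of clinicians, or 26/(100 + 50 + 26) = 14.8% if supervisors are counted. Enrolment of this group continues.

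**3. The test.** Bartholomew's statistic is E² = Σ n_g(m*_g − m)² / total sum of squares. Here m is the grand mean, and the m*_g are the group means after pooling neighbours that violate CM ≥ LC ≥ second generation ≥ DE. The null is that all means are equal.

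**4. Simulation.** Assumed: independent normal change scores, SD 1, no clustering, 40,000 runs per scenario. The 5% critical value was simulated under equal means (0.0249 and 0.0361). The article gives no split by arm, so two sets of sizes (CM/LC/second generation/DE) were used: clinicians plus supervisors divided equally, 50/50/26/50, and clinicians only, 33/33/26/34.

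| True means CM / LC / 2nd gen / DE | Rejects, 50/50/26/50 | Rejects, 33/33/26/34 |
|---|---|---|
| 0 / 0 / −0.5 / 0 | 20.2% | 21.2% |
| 0 / 0 / −0.8 / 0 | 40.5% | 43.5% |
| 0 / 0 / +0.5 / 0 | 7.1% | 7.5% |
| 0.5 / 0.5 / 0.5 / 0 | 85.3% | 69.9% |
| 0.25 / 0.5 / 0.25 / 0 | 59.8% | 43.2% |

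**5. Why row 1 rejects.** The randomized arms are equal. A low second-generation mean is pooled with DE: (26 × −0.5 + 50 × 0)/76 = −0.17, or (26 × −0.5 + 34 × 0)/60 = −0.22. The test then sees CM and LC above a lower block, which fits the stated order.

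**6. What rejection says about CM and LC.** In row 4, CM equals LC and only DE is low. A direct one-sided 5% test of CM over LC rejects in 5.1% and 5.2% of runs, against 85.3% and 69.9% for the ordered test. In row 5, LC is truly better than CM; among the runs that reject, the observed CM mean is below LC in 88.8% and 83.4%.

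**7. Removing the fourth group cures only the first problem.** With three arms and CM = LC, both 0.5 SD above DE, Bartholomew's test rejects in 84.4% (50 per arm) and 69.3% (33 to 34 per arm). CM versus LC still needs its own estimate.

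**The case against.** The strongest reply is that the text is loosely worded rather than wrong in design. The Aim 1 heading names three conditions, the later comparison of second-generation clinicians is close to what a reviewer would ask for, and the Missing data section defines inclusion by randomized condition. A directional test for a directional hypothesis is a legitimate choice, and pairwise contrasts are usually left to the analysis plan. This stands as far as it goes, but the stated test still says four groups, and Aims 1 and 3 disagree on the fourth.

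Some stronger readings are tempting, and the document does not support them.
- *Second-generation staff are treated as independent of the colleagues beside them.* Aims 1 and 3, Proposed statistical analyses and Nesting all promise to account for nesting.
- *These staff are self-selected, or exist only where PCIT was kept going.* How they are chosen is not described. It is documented only that they were never an allocated condition and arise after randomization. Individual first-generation clinicians were not randomized either; their counties were.
- *The article claims that rejection proves every step of the ranking.* It states the ranking as a hypothesis and does not say this.
- *An advantage for DE or LC could not emerge.* The ordered test has almost no power for a DE advantage, but the model under Nesting has an effect for each condition, and its estimates would show one.
- *Aim 2 misuses the test because it does not rank CM against LC.* An ordered test can take a partial order such as LC and CM both above DE, and for penetration the article names only the one-way ANOVA of Aim 1.

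**Conclusion.** The point holds in two parts. First, the stated main test for Aim 1, carried into Aim 3, contains a group that was never allocated and forms after randomization, and the two aims define that group differently. With the randomized arms equal, an assumed 0.5 SD deficit in that group alone brings rejection to about 20% to 21% at a nominal 5%; at 0.8 SD it is 41% to 44%. If the group is better rather than worse by 0.5 SD, the rate is only 7% to 8%. Second, rejection by Bartholomew's test does not by itself establish CM over LC: with CM equal to LC and DE 0.5 SD lower, it rejects in 70% to 85% of runs.

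The percentages rest on assumed group sizes, assumed effects and independent observations. The direction of both conclusions does not: the first follows from the allocation and the second from the definition of the test. The passages should be reconciled before analysis.

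**What to change.** - Run the main Aim 1 and Aim 3 test on first-generation clinicians, and on their dyads, in LC, CM and DE, each counted in the condition of the county. Replace the reference to four groups accordingly.
- Keep Bartholomew's test on the three conditions if wished. Report the CM-LC, CM-DE and LC-DE differences with two-sided confidence intervals from the mixed model already planned, and draw no conclusion that CM exceeds LC from the ordered test alone.
- Analyse second-generation staff and their dyads separately, labelled as a non-randomized comparison. The later analysis in Aim 1 can serve for this. Use one definition, either CM- and LC-trained or CM-trained only, in both aims.

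The cost is wording and no new data. Second-generation data leave the main test. The CM-LC interval may be wide: before clustering its half-width is about 1.96 × √(2/50) = 0.39 SD with 50 per arm, or 1.96 × √(2/33) = 0.48 SD with 33. A two-sided 5% test of an assumed 0.5 SD CM-LC difference has 71% or 53% power at those sizes. Replacing the ordered test by Holm-adjusted pairwise tests is not required and would cost more. In a simulation with 17 per arm and true means 0.9/0.45/0 SD for CM/LC/DE, any rejection fell from 80% to 60%.
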